### 9.3 Multivariate analysis

Not applicable.

**9.4 Interim analysis (if applicable)**

Not applicable.

## 10 ETHICAL CONSIDERATIONS

### 10.1 Regulation statement

The study will be conducted according to the principles of the Declaration of Helsinki (2008) and in accordance with the Medical Research Involving Human Subjects Act (WMO).

### 10.2 Recruitment and consent

Recruited will take place within (i) SEARCH, the network of mental health institutions within Limburg and South Brabant, (ii) general practices and (iii) the general population.

Subjects will be made aware of the possibility to participate in this study by their supervising care givers. Subjects from the general practices and general population will be recruited through posters in drugstores and general practices. Subject will either contact the researcher themselves in case they want to participate or their supervising care giver will contact the researcher. In case subjects show interest they will be invited by the investigator of this study who will provide them with all information about the study and risks, benefits and rights of participants. Subjects have a week to decide whether or not they want to participate. In case a subject does not want to participate, but changes his/her mind later, he or she can still participate.

### 10.3 Objection by minors or incapacitated subjects (if applicable)

Not applicable. Only adults (>18 years) and capacitated individuals will be included in the study.

### 10.4 Benefits and risks assessment, group relatedness

There are no health risks associated with the research.

A personal benefit is that the subject may gain increased insight and control over his/her mechanisms of vulnerability and recovery.

A second personal benefit for the subject is that the standard treatment can be adapted to the individual needs since the therapist can use the feedback to assess the patients' development and determine further treatment goals.

There is a third benefit in that the information on (change in) daily life person-context interactions available for the patient and therapist during antidepressant treatment is hypothesized to positively influence treatment efficacy in both the short- and long-term.

Furthermore, the continuous monitoring during treatment of these person-context interactive phenotypes, which have been shown to be predictive for risk and recovery of

depression, may improve the assessment of treatment response and help clinicians in the estimation of further treatment goals for the particular patient.

When the intervention results in an improvement in treatment efficacy and can be implemented in general mental health care, the benefits for health and quality of life are expected to far outweigh the costs of this study. The cost-effectiveness of the intervention will be explicitly examined. The benefits for society imply a considerable reduction in both the costs of healthcare consumption, the burden on the health care system, and the costs of loss of productivity due to the illness.

Subjects from both control conditions will not be offered the experimental intervention after finishing the study, given the experimental phase of the study.

Burden for the patients is investment of time. After a screening procedure in which subjects have to undergo a psychiatric interview, fill out some questionnaires, and also have to spit some saliva in a tube (total of 3 hours), time investment for subjects is 5.5 hours for questionnaires (distributed over 7 meetings). In addition, all subjects participate twice in the MET-D measurements (5-day period of filling in diaries concerning daily life events and mood), which will take approximately 4 hours in total. MET-D measurement takes place in the actual living environment of the patient during which they engage in their normal daily activities, and as such reduces the burden for the patient. Before the start of the MET-D measurements, subjects have to come in for a short meeting of approximately 40 minutes to receive specific instructions related to this procedure and the MET-D device. Subjects in both experimental groups have to complete the MET-D measurements for 3 days a week during a 6-week period, and have weekly contact with the researchers during this 6-weeks period.

In sum, the investment of time after screening procedures and MET-D instruction comprises for all subjects 10 hours. For both experimental groups (MET-D intervention with and without feedback), participation will take an additional 13.5 hours.

### **10.5 Compensation for injury**

The sponsor/investigator has a liability insurance which is in accordance with article 7, subsection 6 of the WMO.

The sponsor (also) has an insurance which is in accordance with the legal requirements in the Netherlands (Article 7 WMO and the Measure regarding Compulsory Insurance for Clinical Research in Humans of 23rd June 2003). This insurance provides cover for damage to research subjects through injury or death caused by the study.

1. € 450.000,-- (i.e. four hundred and fifty thousand Euro) for death or injury for each subject who participates in the Research;
2. € 3.500.000,-- (i.e. three million five hundred thousand Euro) for death or injury for all subjects who participate in the Research;
3. € 5.000.000,-- (i.e. five million Euro) for the total damage incurred by the organisation for all damage disclosed by scientific research for the Sponsor as 'verrichter' in the meaning of said Act in each year of insurance coverage.

The insurance applies to the damage that becomes apparent during the study or within 4 years after the end of the study.

#### **10.6 Incentives (if applicable)**

Subjects are fully compensated for any travel expenses related to the study.

## 11. ADMINISTRATIVE ASPECTS AND PUBLICATION

### 11.1 Handling and storage of data and documents

Data are handled confidentially and if possible anonymously. The data are coded using a number indicating the order of entry. Only the main investigator ([name]) has permission to access the source data. Where it is necessary to be able to trace data to an individual subject, a subject identification code list is used to link the data to the subject. The key to the code is safeguarded by the investigator. Collected material is coded and will be stored with the purpose of analysis. After material is analysed it will be destroyed. The handling of personal data complies with the Dutch Personal Data Protection Act (in Dutch: De Wet Bescherming Persoonsgegevens, Wbp).

### 11.1 Amendments

*<The following text is applicable for studies without an investigational medicinal product.>*

Amendments are changes made to the research after a favourable opinion by the accredited METC has been given. All amendments will be notified to the METC that gave a favourable opinion.

All substantial amendments will be notified to the METC and to the competent authority.

Non-substantial amendments will not be notified to the accredited METC and the competent authority, but will be recorded and filed by the sponsor.

### 11.3 Annual progress report

The sponsor/investigator will submit a summary of the progress of the trial to the accredited METC once a year. Information will be provided on the date of inclusion of the first subject, numbers of subjects included and numbers of subjects that have completed the trial, serious adverse events/ serious adverse reactions, other problems, and amendments.

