Levels of reward experience, stress sensitivity and affect variability are calculated from the MET-D observations for each subject at the end of each intervention week. Since these are complex phenotypes derived from combinations of data they are not subject to easy conscious manipulation by patients.

Before entering the study, subjects will be screened for a current depressive episode by means of the Structured Clinical Interview for DSM-IV Axis I Disorders (SCID-I) and the Hamilton Depression Rating Scale (HDRS). After inclusion, a saliva sample will be taken for genetic analysis and the subject has to complete the following measurements: Inventory of Depressive Symptoms (IDS) [31], the NEO personality inventory (NEO-PI-R) [32, 33], Childhood Trauma Questionnaire (CTQ) [34], Interview for Recent Life Events (IRLE) [35], Empowerment Questionnaire [36], TiC-P (Trimbos/iMTA questionnaire for Costs associated with Psychiatric Illness) [37], PRODISQ (PROductivity and DISease Questionnaire) [38], and EQ-5D (Euroqol-5D) [39]. Because we hypothesize that the effect of the MET-D feedback on reward experience results in an increase in of empowerment of the subjects, the Empowerment Questionnaire will be used as an additional measurement of the effect of the MET-D intervention. The latter three questionnaires (TiC-P, PRODISQ and EQ-5D) will be used in the costs-efficacy analysis of the MET-D.

All subjects receive additional MET-D training on a separate moment. All groups receive the following pre and post intervention measurements: i) SCID-I interview for diagnosis of depression, ii) HDRS, and iii) IDS. In addition, there are four follow-up measurements of SCID, HDRS and IDS for all groups at 4, 8, 12 and 24 weeks after the end of the intervention, and two follow up measurements of TiC-P, PRODISQ, and EQ-5D for all groups at 12 and 24 weeks after the intervention (see table 1).

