### 4.4 Sample size calculation

Three groups of 40 patients have been chosen since power calculations showed that these sample sizes using repeated measurements yield around 90% power to examine the main hypotheses with power estimates around 88 and 90%. To detect a 3-point difference in HDRS-17 score between the experimental and non-experimental arms with  $\alpha < 0.05$  and  $\beta < 0.10$  we have a power of 0.93. To detect an effect of reward experience or stress sensitivity (OR=0.5) on future relapse with  $\alpha < 0.05$  and  $\beta < 0.10$  we have a power of 0.95. Since we expect a drop-out of around 20 subjects, we will recruit 140 subjects, leaving 120 participants with complete data randomized over three conditions.

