## 7.2 Randomisation, blinding and treatment allocation

Patients are randomly divided into the 'MET-D intervention *with* feedback' group, the 'MET-D intervention *without* feedback' group and the 'control' group.

Randomization takes place after screening procedures.

Subjects are obviously not blind to their treatment allocation, however, they do remain blind as to how ESM measures relate to testing the hypothesis. Since MET-D feedback will be given to the therapist as well, the therapist is also not blind to the treatment allocation.

In order to check that the HDRS ratings by the researcher are not biased by the researcher's knowledge of the participant's condition, we compare IDS scores with HDRS ratings. The IDS is a self-report measure with similar item content compared to the HDRS and is proven highly related to clinician's rated HDRS score.

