All subjects will participate in a second 5-day ESM period, and are again briefed and debriefed with respect to this procedure. Before and after the 5-day ESM period, all subjects again undergo the psychiatric interviews (the depression part of the SCID-I and HDRS) and have to complete the self-report questionnaire concerning depressive symptoms (IDS). The Empowerment Questionnaire has to be completed by all subjects before the 5-day ESM period as well.

Follow up period:

For all subjects, follow-up measurements of SCID-I and HDRS take place at 4, 8, 12 and 24 weeks after the end of the intervention. The follow-up of the Recent Life Event Scale will take place at 12 weeks after the intervention. The follow up of TiC-P, PRODISQ, and EQ-5D will take place at 12 and 24 weeks after the intervention.

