#### **7.4 Withdrawal of individual subjects**

Subjects can leave the study at any time for any reason if they wish to do so without any consequences. After consulting the independent physician, the investigator can decide to withdraw a subject from the study for urgent medical reasons. Subjects refusing collection of a saliva sample can still participate in the study if the wish to do so.

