**7.6 Follow-up of subjects withdrawn from treatment**

The number of withdrawals, and reasons for withdrawal will be reported in the publication of the study. It will be examined whether these subjects differ in any characteristics from those that do not withdraw.

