**8. SAFETY REPORTING**

Not applicable

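### Section 8 sets safety reporting aside, yet section 11.3 promises the ethics committee yearly data on serious adverse events that no procedure systematically collects

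*Protocol*

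**What the plan says.** Two sections of the protocol deal with safety reporting.

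- Section 8 (Safety reporting) has no subsections and reads in full "Not applicable".
- Section 11.3 (Annual progress report) requires a yearly summary to the accredited ethics committee. Its contents include "serious adverse events/ serious adverse reactions, other problems, and amendments". The sentence carries no condition and is not marked as optional.

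The parts that describe what is done to patients are these.

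- Section 7.3: "follow-up measurements of SCID-I and HDRS take place at 4, 8, 12 and 24 weeks after the end of the intervention". Section 3 adds the IDS at the same times.
- Section 3 also provides for "two follow up measurements of TiC-P, PRODISQ, and EQ-5D for all groups at 12 and 24 weeks after the intervention". It assigns these instruments to the economic analysis.
- Section 7.4: after consulting an independent physician, "the investigator can decide to withdraw a subject from the study for urgent medical reasons".
- Section 7.6: "The number of withdrawals, and reasons for withdrawal will be reported in the publication of the study". Withdrawn patients are also compared with the others on their characteristics.

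The Summary and section 10.4 state that the research carries no health risk.

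**The concern.** Section 8 tells site staff that there is nothing to report, while 11.3 obliges someone to report serious events each year. The author of that report has no defined source to draw on. The protocol gives no definition of an event, no question to the patient, no period over which events count and no route from the person who hears of one to the person who writes the report.

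The population makes this more than a clerical matter. Section 4.2 admits patients with current major depression, or past depression with residual symptoms, all on antidepressants. Suicide attempts, deaths and admissions are what an ethics committee would most want to hear about. What is at stake is patient oversight and a commitment to the committee, not the efficacy analysis.

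**Working it through.** The plan gives no figure to reproduce. The check sets the sections side by side and counts scheduled contacts.

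**1. Does any text reconcile sections 8 and 11.3?** Apart from 11.3, adverse-event terms appear only as expanded entries in the abbreviation list. Nothing limits 11.3 to events caused by the study: it names serious adverse events as well as serious adverse reactions. The two sections conflict as written.

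**2. Could another procedure supply the data?**

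- SCID-I (depression part), HDRS and IDS: they capture worsening of symptoms. They are not described as a record of attempts, admissions or deaths.
- Medication monitor (Time frame legend, section 3): it bears on drug use, and no link to 11.3 is stated.
- TiC-P: it may pick up some admissions, but as cost data. Its items and recall period are not described.
- Weekly sessions in arms 1 and 2: the debriefing described in section 3 concerns the MET-D measurements.
- Reasons for withdrawal (7.6): these go to the publication, and under 11.4 the final report with any publications reaches the committee within a year after the study ends. This is a route, but a late one, and it covers only events that lead to withdrawal.

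None of these is a systematic enquiry, and none is given a path into the yearly report.

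**3. Scheduled all-arm assessments after the intervention.** Section 7.3 places clinical interviews both before and after the second 5-day MET-D period, then at 4, 8, 12 and 24 weeks.

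- Assessments: 2 + 4 = 6.
- With the TiC-P: 2 (weeks 12 and 24).
- Without it: 6 − 2 = 4. These four still have the symptom measures, and the legend groups the medication monitor with those measures.

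**4. Contact by arm.** During the six intervention weeks, arms 1 and 2 have one researcher session a week, so six sessions. Arm 2 also has two added interviews each week on anxiety and depression. No such sessions are described for arm 3. Events left to chance discovery are therefore likelier to surface in arms 1 and 2.

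**5. Time under study.** Intervention plus follow-up is 6 + 24 = 30 weeks per patient, leaving out the two 5-day periods.

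- 120 patients: 120 × 30 = 3,600 patient-weeks; 3,600 / 52.18 ≈ 69 patient-years.
- 140 patients with no drop-out: 140 × 30 = 4,200 patient-weeks; 4,200 / 52.18 ≈ 80 patient-years. This is an upper bound.

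This is observation time, not a count of missed events. The protocol gives no event rate.

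**6. Patients who leave.** Section 4.4: "Since we expect a drop-out of around 20 subjects, we will recruit 140 subjects". That is 20 / 140 = 14.3%. No assessment after withdrawal is described for them.

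**The case against.** The best defence is that this is a low-risk study. It adds diaries, feedback and interviews to usual care, and section 10.4 sees no health risk. Template remarks survive in sections 5, 6 and 11, so the clash may simply be two template blocks that were never aligned. Researchers interview every patient repeatedly, and 11.3 itself gives them a reason to note a serious event they hear of.

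Much of this stands. The risk statement plausibly explains section 8, and events that come to notice can be reported. It does not remove the conflict, because 11.3 is current and unconditional and covers events whatever their cause.

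A reader might go further and infer that the 11.3 report cannot be produced at all, or that a suicide attempt or death has no route whatever to the committee. The protocol does not support either reading. An event that leads to withdrawal falls under 7.6 and reaches the committee through the final report in 11.4, and urgent medical withdrawals involve the independent physician. The gap is narrower: systematic and timely capture, above all of events in patients who stay in the study and of events after withdrawal.

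Nor is this something commonly left to a statistical analysis plan. Collecting and reporting serious events is study conduct, and this protocol has a section for it.

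**Conclusion.** The contradiction is real and should be corrected. As written, the protocol cannot deliver systematically what 11.3 promises. Existing measures would reveal some serious events, but late, incompletely and unevenly between arms.

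The size is best given by the schedule. No planned question on serious events exists at any of the six post-intervention assessments, and only two of the six carry even the TiC-P. The 69 to 80 patient-years of observation must not be read as a measure of events missed; the number of events is unknown.

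A reader might also suspect bias in the efficacy results. The documents do not support this: no endpoint or planned comparison uses adverse-event data.

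The conclusion rests on two assumptions. The time-frame figure, which is not shown, is taken to contain no safety enquiry beyond its legend, which lists none. The sentence in 11.3 is taken as intended; if it is a template leftover, the conflict with section 8 still needs resolving.

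**What to change.** Replace the entry in section 8 with a short rule.

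- **Definition and period.** A serious adverse event is, at minimum, a death, a suicide attempt or a hospital admission, from randomisation to the 24-week follow-up, whether or not it seems related to the study. The sponsor may widen the list. Section 7.2 fixes the start: "Randomization takes place after screening procedures".
- **Enquiry.** Ask one fixed question in all three arms at the last post-intervention visit (after the second 5-day period) and at 4, 8, 12 and 24 weeks. The first covers the time since randomisation, each later one the time since the previous enquiry. Ask it also at withdrawal. Scheduled ascertainment then no longer depends on the weekly sessions.
- **Other sources.** Record events learned of at a weekly session, from a therapist or through the TiC-P, with date and source.
- **Relatedness.** The investigator judges whether each event is related to study procedures. Without this the serious adverse reactions named in 11.3 cannot be reported as such.
- **Report.** List all events in the 11.3 report.

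The cost is one short question at five existing visits, 5 × 120 = 600 to 5 × 140 = 700 in all, plus one at each withdrawal (about 20), and a paragraph of text. Contact after withdrawal, with the patient's permission, would close the remaining gap but is optional.

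Deleting the safety items from 11.3 would also end the contradiction, but it would leave the oversight gap open.

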### 11.4 End of study report

*<The following text is applicable for studies without an investigational medicinal product.>*

The investigator will notify the accredited METC of the end of the study within a period of 8 weeks. The end of the study is defined as the last patient's last visit.

In case the study is ended prematurely, the investigator will notify the accredited METC, including the reasons for the premature termination.

Within one year after the end of the study, the investigator/sponsor will submit a final study report with the results of the study, including any publications/abstracts of the study, to the accredited METC.

**11.5 Public disclosure and publication policy**

Results of this study will be published in peer-reviewed international scientific journals.

Both positive and negative results will be published. There are no restrictions in the public disclosure of scientific findings resulting from this study

